## Abstract

**Background:**

Technological innovations in dental materials have been fueled by the desire of patients to improve the esthetics of their teeth. This emphasis on esthetics has led dentists to seek resources that respect the standards established by society, but without compromising the integrity of the teeth.

**Methods/design:**

The aim of the proposed controlled clinical trial will be to assess colorimetric changes and increased dental sensitivity in adolescent patients submitted to tooth whitening with 6% and 7.5% hydrogen peroxide using home kits with whitening strips. Adolescents aged 12 to 20 years will be allocated to different groups based on treatment (*n* = 16 per group): (1) placebo; (2) 6.0% hydrogen peroxide (White Class with Calcium, FGM); (3) 7.5% hydrogen peroxide (White Class with Calcium, FGM); and (4) 7.5% hydrogen peroxide (Oral B 3D White, Oral-B). After the whitening procedures, the participants will be evaluated using a visual analog scale for tooth sensitivity and digital spectrophotometry to measure changes in color. Descriptive analysis of the data will be performed. Either the chi-squared test or Fisher’s exact test will be used for the determination of associations among the categorical variables. Student’s *t*-test and analysis of variance will be used to compare mean colorimetric data. Pearson’s correlation coefficients will be calculated to determine the strength of correlations among the continuous variables.

**Discussion:**

This randomized trial will provide an opportunity to evaluate products such as whitening strips in comparison to other self-administered methods, especially in adolescents.

**Trial registration:**

The protocol for this study was submitted to Clinical Trials in November 2013 with registration number NCT01998386.

## Background

Technological innovations in dental materials have been fueled by the desire of patients to improve the esthetics of their teeth, which many consider to be an important aspect of quality of life [1, 2]. This emphasis on esthetics has led dentists to seek resources that respect the standards established by society, but without compromising the integrity of the teeth, as the treatment philosophy should be the maximum preservation of sound dental tissues [3, 4].

Tooth discoloration is classified based on the etiology. Extrinsic factors cause superficial changes in color, such as staining due to the consumption of coffee, tea, soft drinks, etc. Intrinsic factors, whether congenital or acquired, cause more complicated discoloration that is difficult to treat, as such discoloration is incorporated into the structure of the teeth and generally only removed through the use of more aggressive procedures that can have a negative effect on sound dental tissues [3, 5, 6].

Esthetic problems in childhood and adolescence can exert a significant influence on one’s psychosocial development and interactions with peers. Shulman *et al*. [7] evaluated 2,495 patients and found that 32% of the children were dissatisfied with the color of their teeth and 19% of the parents shared this dissatisfaction. Indeed, children, adolescents and young adults have become increasingly concerned with dental esthetics, which may have an important psychological impact on quality of life and may be one of the driving forces behind the current demand for dental materials and noninvasive procedures aimed at improving tooth color [8].

Tooth whitening is the procedure most commonly employed by professionals and patients and is considered the least invasive esthetic treatment for improving the appearance of one’s smile. The procedure is simple and inexpensive. However, the expected whitening outcome cannot be guaranteed [1–3].

Whitening can be performed in the dentist’s office or with the use of a home kit [3]. At-home whitening should be supervised by a dental professional and consists of the application of different concentrations of a peroxide gel (carbamide or hydrogen) to the teeth with the aid of personalized molds [9].

The desires of consumers, fueled to some extent by the standards of beauty dictated by society [1], have stimulated the development of over-the-counter products sold in pharmacies and supermarkets without the need for a prescription or professional supervision [1, 10, 11]. These whitening products first appeared in the USA in 2000 as an alternative to dental staining treatment, with a lower cost in comparison to traditional treatment by dentists [10]. In the last 10 years, other over-the-counter whitening agents have been added, such as toothpastes, mouthwashes and chewing gum [10].

Whitening strips and varnishes containing peroxide fall into this category of freely commercialized products without professional supervision, exposing individuals to allergic reactions, the ingestion of the whitening agent and dental sensitivity [12, 13]. Moreover, the lack of professional monitoring indicates there may be a greater risk of the improper use of these products [11].

The safety, efficacy, long-term color stability and discomfort (dental sensitivity and gingival irritation) of over-the-counter whitening products need to be evaluated, quantified and described in the scientific literature. Thus, long-term controlled clinical trials are needed to evaluate products such as whitening strips in comparison to other self-administered methods, especially for adolescents.

The aim of the proposed study is to broaden knowledge of the clinical use and characteristics of self-administered hydrogen-peroxide-based whitening materials for professional use and over-the-counter sales employed and indicated for adolescents aged 12 to 20 years.

### Specific objectives

The specific objectives are to:
Evaluate and quantify colorimetric changes in young permanent anterior teethCompare the efficiency and efficacy of three gels used for self-administered home whitening and an over-the-counter whitening stripAnalyze the increase in dental sensitivity for adolescent patients undergoing home whitening with 6% and 7.5% hydrogen peroxide with and without the addition of calcium (whitening strips)Assess sensitivity, comfort and acceptance of whitening strips by patientsAssess patient satisfaction with the method and material used for home whitening

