**Table 1 Tab1:** **Summary of experimental conditions**

Group	Presence or absence of change in tooth color	Application site	Treatment
1	Presence	Maxillary and mandibular anterior teeth	Placebo gel without hydrogen peroxide - Formula e Açao – Sao Paulo/SP
			- without activating source
2	Presence	Maxillary and mandibular anterior teeth	6.0% hydrogen peroxide –White Class with Calcium, FGM – Joenville/SC
			- without activating source
3	Presence	Maxillary and mandibular anterior teeth	7.5% hydrogen peroxide –White Class with Calcium – FGM – Joenville/SC
			- without activating source
4	Presence	Maxillary and mandibular anterior teeth	7.5% hydrogen peroxide – Oral-B 3D White, Oral-B - EUA
			- without activating source

For each group, 16 individuals enrolled at the Dental Clinic of the University Nove de Julho will be selected. After receiving all necessary information regarding the study, including the procedures and possible risks, the volunteers who agree to participate and their respective guardians will sign a statement of informed consent.

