### Tooth whitening method using 6.0% or 7.5% hydrogen peroxide gel

Castings will be made of the volunteers’ upper and lower arches and plaster will be poured into the molds. Individual plastic molds (vacuum formed, flexible acetate 1 mm in thickness) will be made for each arch using the plaster models. After fitting the molds in the oral cavity, the volunteers will receive oral and written instructions on how to use the whitening gel and will be instructed to perform proper oral hygiene with dental floss and a toothbrush prior to the application of the whitening agent. The volunteers will be instructed to use the molds with whitening gel (6.0% or 7.5%, depending on which group the volunteer is in) one hour a day for 7 days.

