### Tooth whitening using whitening strips

The participants in this group will receive four disposable whitening strips for daily individual use. The volunteers will be instructed to perform proper oral hygiene with dental floss and a toothbrush prior to the application of the whitening strips. The volunteers will receive oral and written instructions on how to use the whitening strips, which will be placed on the surface of the teeth for 30 minutes twice a day for 7 days.

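### The third objective names hydrogen peroxide with and without calcium, but the four arms cannot separate calcium from the rest of the strip product

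*Protocol article*

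**What the plan says.** The protocol article, under Specific objectives, lists as its third objective the analysis of increased sensitivity in adolescents whitening at home "with 6% and 7.5% hydrogen peroxide with and without the addition of calcium (whitening strips", where the parenthesis closes. The second objective, just before it, compares three gels with an over-the-counter strip.

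The abstract and Table 1 define four arms:

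- Group 1: "Placebo gel without hydrogen peroxide" (Table 1).
- Group 2: "2) 6.0% hydrogen peroxide (White Class with Calcium, FGM" (abstract).
- Group 3: "3) 7.5% hydrogen peroxide (White Class with Calcium, FGM" (abstract).
- Group 4: "4) 7.5% hydrogen peroxide (Oral B 3D White, Oral-B" (abstract).

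The section on the 6.0% and 7.5% gels has them worn in individual plastic molds "one hour a day for 7 days". The placebo gel has the same molds and schedule. The section on whitening strips describes the remaining arm, Group 4, with strips "which will be placed on the surface of the teeth for 30 minutes twice a day for 7 days".

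The abstract's statement of aim, however, speaks of "tooth whitening with 6% and 7.5% hydrogen peroxide using home kits with whitening strips".

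**The concern.** The wording of the third objective names two factors, concentration and the addition of calcium, and so invites a reader to expect an answer on each. For calcium, that would need at least one pair of arms alike in everything except calcium, and a pair at each concentration if the phrase is taken to cover both.

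If no such pair exists, a difference in sensitivity between the calcium gel and the strip could be read as evidence about calcium when it may come from the device, the rest of the formulation or the way the product is applied. What is at stake is the conclusion that the trial may draw on this objective. The arms, the sample size and the planned tests are not affected.

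The abstract adds to the confusion. A reader who relies on it would think that 6% and 7.5% peroxide were both given by strip, in which case device would not differ between the concentrations or between the calcium conditions.

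**Working it through.** No figure in the article bears directly on this point. The sample size (16 per group, 19 with the allowance for losses) does reproduce. With a difference of 2.8, standard deviation 2.1, two-sided 5% error and 95% power, a two-sample t-test needs 15.65 per group, rounded up to 16, and 16 × 1.15 = 18.4 rounds up to 19. That calculation concerns a difference in W, not sensitivity, and a larger sample would not change what follows.

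**Step 1: cross the two factors named in the objective.** Inputs: the arm list in the abstract and Table 1.

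| | With calcium | Without calcium |
|---|---|---|
| 6% | Group 2 | no arm |
| 7.5% | Group 3 | Group 4 (inferred) |

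One of the four cells is empty, so nothing can be said about calcium at 6%. Group 4 is placed in the last cell by inference: calcium appears in the names of the FGM gels only, and the objective's parenthesis seems to label the calcium-free condition as the strip. The article does not say outright that the strip has no calcium.

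Group 1 cannot fill the gap, because it contains no peroxide. Its later 6.0% gel, given 30 days after the start of treatment, cannot either: that gel's calcium content is not stated, and it is not a concurrent randomized arm.

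**Step 2: list what changes among the peroxide arms.** Inputs: Table 1 and the sections on the gel and strip methods.

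| Attribute | Group 2 | Group 3 | Group 4 |
|---|---|---|---|
| Calcium absent (inferred for Group 4) | 0 | 0 | 1 |
| Strip, not mold | 0 | 0 | 1 |
| Oral-B, not FGM | 0 | 0 | 1 |
| Two sessions a day, not one | 0 | 0 | 1 |

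The four rows are identical. Write the mean sensitivity difference, Group 4 minus Group 3, as

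C + D + M + P,

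with C for absence of calcium, D for device, M for the remaining manufacturer and formulation differences, and P for application pattern. The data give one value for the sum of four unknown terms, and any interactions add more. Group 2 against Group 3 holds all four attributes fixed, so it says nothing about any of them. Group 4 against Group 1 changes peroxide as well as device, so it adds a further unknown instead of removing one. Calcium is completely aliased with the product.

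**Step 3: check exposure.** Gel: 1 × 60 = 60 minutes a day. Strip: 2 × 30 = 60 minutes a day. Over 7 days each gives 60 × 7 = 420 minutes. Nominal contact time is matched; only its division into sessions differs.

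**Step 4: check the abstract's aim against the methods.** The aim links both concentrations to strips. The methods put the 6.0% gel and the FGM 7.5% gel in molds. Only Group 4 uses strips, and no 6% strip exists in this trial.

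**The case against.** The best defense is that the third objective was never meant to isolate calcium. Its verb is to analyze, not to compare, and the parenthesis may only label which product is the calcium-free one. On that reading it is a compressed list of the materials in which sensitivity will be described, and the four arms with repeated visual analog readings can deliver that. The general aim in the Background and the second objective are both framed as comparisons of products. The statistical section names no calcium contrast, and the Discussion offers no hypothesis about calcium. A full factorial of concentration by calcium is not stated anywhere.

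Much of this stands, and it rules out several stronger readings that a reader might infer:

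- *The objective is unanswerable.* Not so. Read as sensitivity by product, it can be met.
- *A difference between Groups 3 and 4 will be reported as a calcium effect.* No section says so.
- *The strip and gel groups have different exposure times.* Daily contact time is equal; only the pattern differs.
- *The lack of a placebo strip, or the fact that participants can see their device, breaks the plan.* No objective promises a placebo-matched comparison for strips, so these contradict nothing stated.

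What the defense does not remove is the wording. The second objective already covers the product comparison. The third singles out the addition of calcium and attaches it to both concentrations. If only products were meant, the phrase says something else. Nor can an unseen analysis plan settle it, because analysis cannot supply a missing arm or undo complete aliasing. If the strip did contain calcium, there would be no calcium-free peroxide gel or strip among the randomized arms at all, and the phrase would fit the design even less well.

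**Conclusion.** The point holds as a mismatch between the wording of an objective and the arms. A calcium effect cannot be estimated at 6%, where there is no calcium-free arm. At 7.5% it cannot be separated from device, manufacturer and formulation, and application pattern, which all change with it in the one contrast available. This is true at any sample size.

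The conclusion about 7.5% assumes that the strip is calcium-free, which is inferred and not stated. It does not extend to the trial as a whole: comparisons between products remain valid, and so does Group 2 against Group 3 for concentration within one gel line and one type of mold.

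The abstract's aim is a separate, plain inconsistency with Table 1 and the method sections. Those sections make clear which product is used where, so it misleads only a reader who stops at the abstract.

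The correction should be made before results are interpreted. The Trial status section reports that recruitment and color evaluation are under way.

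**What to change.** Reword the third objective as contrasts between the products actually given:

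- Group 2 against Group 3: peroxide concentration, within the same gel line and type of mold.
- Groups 2 and 3 against Group 1: active gel against placebo gel.
- Group 3 against Group 4: mold-and-gel product against strip product, as whole products.

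Add two sentences: that no conclusion about calcium will be drawn, and that Group 4 against Group 1 differs in delivery device as well as in peroxide. In the abstract, reword the aim so that only Group 4 is described as using strips, in agreement with the method sections.

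The cost is wording only. No arm, participant, visit or application schedule changes. The sponsor gives up a statement about calcium that the design could not have supported.

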## Materials/design

The present study will be conducted in compliance with the guidelines stipulated for research involving human subjects. It has received approval from the Human Ethics Committee of University Nove de Julho (Brazil), under process number 410.582. Legal guardians will receive information on the objectives and procedures and those agreeing to the participation of their sons and daughters will sign a statement of informed consent.

### Participants

Male and female adolescents enrolled at the Dental Clinic of University Nove de Julho (Sao Paulo, Brazil) will be recruited.

#### Inclusion criteria

Participants will be aged 12 to 20 years, with a diagnosis of altered color on maxillary and mandibular anterior teeth with initial color equivalent to A2 on the Vita scale (Vita Zahnfabrik) and will have a signed statement of informed consent.

#### Exclusion criteria

Participants will be excluded if: they have any dental anomalies (malformation, carious lesions, fractures); they have at least four maxillary and/or mandibular anterior teeth; they have had a known adverse reaction to peroxide; they have used whitening agents (administered in a dental office or at home) in the previous year; they are currently undergoing orthodontic treatment, orthopedic treatment of the jaws or psychological treatment; or they are using medication that can alter the color of the teeth, such as ferrous sulfate.

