### Colorimetric evaluation

The tooth color of all participants will be evaluated before and after the whitening procedures. Color readings of the vestibular region of the maxillary and mandibular anterior teeth will be performed by a previously trained examiner blinded to the allocation of the volunteers to the different groups. A digital spectrophotometer will be used for the colorimetric evaluation.

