### Calculation of sample size

Considering a difference of 2.8 in *W*, 95% power, 5% error and standard deviation of 2.1 based on data from the literature [15], a minimum of 16 participants are needed for each group (see Table 1), to which 15% will be added to compensate for possible losses, totaling 19 volunteers per group. This calculation was made using the STATISTICA program.

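### An exclusion criterion bars anyone with four or more anterior teeth, which contradicts the inclusion criterion, the treatment site and the color outcome

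*Protocol article*

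**What the plan says.** The list in the Exclusion criteria section of the Protocol article opens with "Participants will be excluded if: they have any dental anomalies (malformation, carious lesions, fractures". Its second item is that "they have at least four maxillary and/or mandibular anterior teeth". The items are separated by semicolons and all depend on the same opening verb, so this one is a ground for exclusion like the rest.

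Elsewhere the article says:

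- **Inclusion criteria:** participants are enrolled "with a diagnosis of altered color on maxillary and mandibular anterior teeth with initial color equivalent to A2 on the Vita scale".
- **Table 1:** the application site is the anterior teeth of both jaws in each of the four groups.
- **Colorimetric evaluation:** "Color readings of the vestibular region of the maxillary and mandibular anterior teeth" form the outcome measurement.
- **Specific objectives:** the first objective is color change in young permanent anterior teeth.

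No other section gives a minimum or maximum number of teeth.

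**The concern.** The trial treats and measures anterior teeth, yet having four or more of them is written as a bar to entry. Almost any adolescent who satisfies the inclusion criterion would also meet this exclusion.

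Eligibility criteria define the population to which the results apply. If staff follow the sentence, they turn away the patients the trial was designed for. If they set it aside, they are applying a tooth-count rule that is not written down. Enrolled participants with four or more anterior teeth then depart from the published criterion, and a reader cannot tell what threshold, if any, was used for patients with several missing or affected teeth. That threshold could also vary between screeners or over the recruitment period.

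**Working it through.** The article attaches no figure of its own to this criterion, so the check is a comparison of the sections and a count.

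**Inputs.** Let U be the number of upper and L the number of lower anterior teeth present. A full anterior dentition is taken as U = 6 and L = 6, 12 in all. This is an anatomical assumption; the article does not state it.

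**Step 1: what inclusion requires.** Altered color on anterior teeth of both arches needs at least one such tooth in each: U ≥ 1 and L ≥ 1, so U + L ≥ 2. This is the lenient reading. If the plural is taken to mean two in each arch, then U + L ≥ 4.

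**Step 2: what the exclusion removes.** With the four counted over both arches together, it removes everyone with U + L ≥ 4.

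**Step 3: who is left.** 2 ≤ U + L ≤ 3. The only possible combinations (U, L) are (1, 1), (1, 2) and (2, 1). Under the stricter reading of inclusion in Step 1, nobody is left.

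**Step 4: does the wording of the count rescue it?** The linking phrase between the two jaws also allows a count per arch.

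| Reading of the exclusion | Removes | Person with (6, 6) |
|---|---|---|
| Four in total | U + L ≥ 4 | excluded, 12 ≥ 4 |
| Four in either arch | U ≥ 4 or L ≥ 4 | excluded |
| Four in both arches | U ≥ 4 and L ≥ 4 | excluded |

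If the rule means four in either arch, those left have one to three teeth per arch, two to six in all. No reading admits the ordinary full dentition, so the contradiction does not depend on how the phrase is parsed.

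**Step 5: is the sample size involved?** No. The planned numbers do not use the criterion. For completeness, they reproduce. With a difference of 2.8, SD 2.1, two-sided 5% error (two-sidedness assumed) and 95% power, a t-test needs 15.65, rounded up to 16 per group. Adding 15% gives 16 × 1.15 = 18.4, rounded up to 19.

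**The case against.** The strongest reply is that this is an evident slip that nobody would apply. The Trial status section says the study is already recruiting and evaluating tooth color, which suggests the clinic is not using the literal rule, although no enrolment count is given. That reply has force on the practical consequence. It does not make the sentence correct, and it does not tell the reader which rule is in use.

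A second reply is that a journal article condenses a fuller protocol. That excuses what is left out. Here a criterion is stated, and it conflicts with the other sections.

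Several stronger readings are tempting, and the article does not support them:

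- **That the criterion is certainly reversed.** This is the most natural explanation. But the neighboring item lists defects of teeth (malformation, caries, fractures), so a lost qualifier such as missing or restored is also plausible. The two explanations define different populations.
- **That the trial cannot enrol, or loses its whole planned sample.** The planned sample is 4 × 16 = 64, or 4 × 19 = 76 with the allowance for losses. These are enrolment targets, not a count of people excluded, and they do not measure the harm. No effect on power, error rate or the treatment estimate has been shown.
- **That those admitted would have too few teeth to measure.** The Colorimetric evaluation section sets no minimum number of teeth for a reading, so this is only an inference.
- **That sites would apply the rule differently.** The Participants section names one dental clinic.

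**Conclusion.** The point stands as an internal contradiction: the exclusion criterion cannot be reconciled with the inclusion criterion, the application site or the color outcome, and nothing else in the article corrects it. Its size under a literal reading, counting over both arches and requiring at least one affected tooth in each, is that only people with two or three anterior teeth remain eligible. The exclusion of a full anterior dentition holds under every parsing of the count.

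The intended rule cannot be recovered from the text. In practice the likely harm is an undocumented threshold for patients with several missing or affected anterior teeth; loss of the target population would follow only if the sentence were applied as written. Correction is still needed, because this is a stated eligibility rule in a trial that is recruiting.

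**What to change.** 1. Correct the item in the Exclusion criteria to the tooth-count rule that was intended, after the sponsor confirms whether a minimum was misplaced or a qualifier was lost.
2. If a minimum was meant, move it to the Inclusion criteria, or word the exclusion as fewer than four. If a qualifier was lost, restore it.
3. In either case, say whether the count is per arch or in total. Moving the present wording unchanged would let someone with four teeth in one arch and none in the other meet the tooth count, although inclusion calls for both arches.
4. Check the corrected rule against the Inclusion criteria, Table 1 and the Colorimetric evaluation so that all four agree.
5. Review participants already screened at the clinic against the corrected rule, and document any who were enrolled or turned away inconsistently with it.

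The cost is a one-line amendment and a pass through the screening log. The sample size and the analysis are not affected.
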